## Discussion

To date, this is the first study that investigates long-term efficacy of KDs and FDs on T2 hyperintense lesion load and clinical measures of disease activity and progression in MS patients. This is also the first study that investigates therapeutic effects of repeated prolonged fasting combined with daily intermittent fasting. There are several reasons for the scarcity of such large-scale, long-term studies. The most prominent reasons are, of course, the high demand of financial and human resources. Further, patients often prefer one particular intervention and are therefore prone to withdraw consent when randomized to an undesired intervention. Once patients have committed to such a study, it is challenging to convey dietary interventions in a way that sufficient motivation is aroused. Only this will ensure dietary adherence for the whole intervention period.

There are some critical aspects of our study design. First, we include patients with any MS medication or no medication. From a methodological point of view, including only patients on the same treatment or untreated patients would have been preferable. However, in light of the variety of available treatment options, we would not be able to recruit a sufficient number of patients with the same medication within an acceptable time span. Furthermore, by including patients with different treatments, putative positive results will be more generalizable. Thus, we decided to include all patients who have been stable on or off treatment for at least 6 months. Stratification only differentiates between treatment and no treatment. Having a stratum for every treatment would have resulted in a sample size too unrealistic to recruit and finance. Besides, transferability to clinical routine is only given if the study population, at least in principle, reflects the clinical routine with its diverse application of different treatment options.

Second, a dietary intervention study cannot be blinded completely. Thus, expectations and observer bias cannot be ruled out. However, we try to minimize bias by not communicating any longitudinal data during the study to patients and study personnel in contact with them. Even more important, MRI analysts who evaluate the primary endpoint are blinded for both clinical data and interventional allocation.

Third, we undertake MRI scans of both the cranium and the spinal cord to evaluate disease activity before study entry in order to prevent selection bias. The study MRI, however, only analyzes the cranium, thereby neglecting spinal cord lesions. This entails the risk of overlooking disease activity. However, newly developing spinal cord lesions in MS are often associated with clinical symptoms. Thus, they would be recorded as a relapse within regular clinical assessments. Furthermore, cerebral lesions are more frequent and, therefore, constitute a reliable marker for disease activity.

Fourth, controlling and ensuring adherence to dietary interventions is rather challenging. This is especially true in an outpatient setting during such a long study period. Some patients might be disappointed with their interventional allocation and surreptitiously include some features of the desired group into their diet. This can only be avoided by close and frequent contact between counselor and patient. Furthermore, changing established dietary preferences can be rather challenging and might lead to compliance issues. Patients with suspected or known lack of compliance are excluded from the per-protocol analysis.

One great strength of our study is that patients in the KD group measure their blood ketones at home. Many other studies with low-carbohydrate–high-fat diets did not verify ketosis, which limits the interpretation of results. Although we do not know the actual concentrations of ketone bodies in the brain, blood ketone concentrations have been shown to drive the brain’s overall metabolic rate [50].

Further strengths are the randomized study design, large sample size, long intervention of 18 months and blinded outcome assessment. Moreover, we focus on both MRI-based measures of disease activity and progression and several patient-related endpoints, such as fatigue, depression and quality of life.

Considering epidemiological and preclinical data, on the one hand, and the lack of clinical data, on the other, this study has the potential to provide essential data on the efficacy of KDs and FDs. By analyzing metabolic markers, oxidative stress and the gut microbiome, we hope to shed some light on the mechanisms that underlie these dietary regimens. A better mechanistic understanding might also be applicable to other neurodegenerative diseases.

In conclusion, KDs and FDs have the potential for a safe and inexpensive complementary treatment option in MS and our study might close the gap between promising preclinical data and the lack of clinical data.

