### Power calculation

Based on the results of other MS studies in our research center in comparable patient cohorts, an average of three new T2 lesions after 18 months is expected in the SD group. Sample size was calculated with the Wilcoxon (Mann–Whitney) rank-sum test and the significance level was adjusted (Bonferroni) for the two comparisons (KD vs. SD and FD vs. SD). With a sample size of 33 patients per group and a two-sided significance level of 0.025, there is a power of 80% to detect a probability of 0.72 that an observation from group 1 is smaller than that from group 2. This corresponds to a standardized effect size of 0.83 and an expected mean difference in the number of new T2 lesions in each of the intervention groups of 0.5 compared to the SD group after 18 months (Query Advisor 7.0). We expect a dropout rate of approximately 10% and therefore plan to enroll 37 patients per group, 111 patients in total.

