### Data analysis

Confirmatory analysis will be conducted based on the intention-to-treat (ITT) population. The aim is to show that KDs and FDs are superior to the SD, meaning that the number of new T2 lesions after 18 months of dietary intervention adjusted for the baseline value is lower in the KD and FD groups than in the SD group. Although the sample size calculation was conservatively based on the Mann–Whitney *U* test, the final analysis of the primary endpoint will be based on non-parametric analysis of covariance (ANCOVA) on ranks with the treatment group as a fixed factor and adjustment for the baseline number of T2 lesions. The resulting coefficients will be reported with 95% confidence intervals and their corresponding *p*-values compared to a two-sided Bonferroni-adjusted significance level of 0.025 [48].

We do not plan any interim analyses. In the case of more than 5% missing for the primary endpoint, we plan to replace missing values in the outcome parameter using multiple imputation [49] under the missing at random assumption in addition to the complete case analyses.

As a sensitivity analysis, the primary endpoint will be analyzed in the per-protocol population. This population includes all randomized patients who meet the study eligibility criteria and fulfill all compliance criteria throughout the study.

We intend to perform two subgroup analyses, men vs. women and MS medication vs. no MS medication, by adding another main effect for sex or medication, respectively, as well as an interaction term. These subgroup analyses will be analyzed in an exploratory manner to generate possible hypotheses for follow-up studies without adjustment for multiple comparisons. For these, *p*-values may not be interpreted as confirmative.

Safety analysis will include calculation of frequencies and rates of adverse and serious adverse events within 18 months of the interventions.

Secondary endpoints will be analyzed in an explorative manner and descriptives will be given using the mean and standard deviation for sufficiently normal distributed metric variables, the median with limits of the interquartile range (IQR: 25th and 75th percentiles) for skewed metric or ordinal data, as well as absolute and relative frequencies for count data.

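### The primary rank ANCOVA omits baseline MS therapy; the sample-size reason given rules out finer strata but not a covariate, and the cost is some precision, not bias.

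*Protocol article*

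**What the plan says.** The Discussion lists four critical aspects of the design. The first is that patients on any MS medication, or none, are included. It says a single-treatment or untreated population would have been methodologically preferable, and rejects that on recruitment grounds. On randomisation it states: "Stratification only differentiates between treatment and no treatment". The reason for stopping there is: "Having a stratum for every treatment would have resulted in a sample size too unrealistic to recruit and finance".

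The Randomization section gives the strata as sex, MS medication (yes or no) and lesion load (below 15, or 15 and above). Their purpose is to spread possible confounders evenly over the diets. Table 1 records medication at every visit, including screening and baseline.

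The Data analysis section fixes the confirmatory model as ANCOVA on ranks "with the treatment group as a fixed factor and adjustment for the baseline number of T2 lesions". No medication term appears in it. Medication (yes/no) enters only an exploratory subgroup model, as a main effect plus an interaction with treatment.

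**The concern.** The protocol treats medication as relevant to outcome in three places: it stratifies on it, it expects larger diet effects in patients without it (Introduction), and it names mixed medication as a design weakness. The confirmatory model then uses none of this information, not even the yes/no factor that governed allocation.

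The stated reason is about the number of strata. It is sound for stratified randomisation, but says nothing about adjustment in the analysis, which the article does not discuss. If new-lesion rates differ between therapies, that variation stays in the residual unless the baseline T2 count happens to carry it. Yes/no stratification also cannot balance drug types among treated patients. If an imbalance appeared, adjusting for it without prior specification would be post hoc.

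**Working it through.** **1. The plan's own figure.** The inputs come from the Power calculation section, which takes a covariate-free rank-sum test, Bonferroni-adjusted for two comparisons, with 33 per group and a two-sided level of 0.025. Its target is given as follows: "there is a power of 80% to detect a probability of 0.72 that an observation from group 1 is smaller than that from group 2".

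- Noether's formula: N = (z₀.₉₈₇₅ + z₀.₈₀)² / [3(p − 0.5)²] = (2.241 + 0.842)² / (3 × 0.22²) = 9.505 / 0.1452 = 65.5. That is 32.7, so 33 per group.
- Power at 33 per group: Φ(√(3 × 66) × 0.22 − 2.241) = Φ(3.096 − 2.241) = 80.4%.
- Effect size: √2 × z₀.₇₂ = 0.824 (stated 0.83).
- Dropout: 33 / 0.9 = 36.7, so 37 per group and 111 in total.

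The stated size reproduces. It contains no covariate, so it does not depend on the point made here.

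**2. What a covariate could be worth.** Let R² be the share of residual rank variance that therapy explains. The article gives no basis for R², so a range is shown. Power at 33 per group is Φ(√(198 / (1 − R²)) × 0.22 − 2.241).

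| Assumed R² | Power | n per group for 80% |
|---|---|---|
| 0 | 80.4% | 33 |
| 0.02 | 81.2% | 33 |
| 0.05 | 82.5% | 32 |
| 0.10 | 84.7% | 30 |
| 0.20 | 88.9% | 27 |
| 0.30 | 92.8% | 23 |

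**3. Simulated rank ANCOVA.** Settings: 33 per arm, control mean 3 (as stated), overdispersed counts. Assumed: 30/40/30% none/group A/group B, diet rate ratio 0.4, 1,500 runs per setting, simple rather than stratified allocation. Power for one diet against SD:

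| Relative lesion rates (none/A/B) | Dispersion | No therapy term | Yes/no | Three levels | Three levels minus yes/no |
|---|---|---|---|---|---|
| 1/1/1 | 0.5 | 88.2% | 87.5% | 87.3% | −0.1 |
| 1/1/1 | 1.0 | 67.0% | 66.7% | 65.6% | −1.1 |
| 1/0.8/0.5 | 0.5 | 82.3% | 82.9% | 83.7% | +0.8 |
| 1/0.8/0.5 | 1.0 | 65.0% | 66.4% | 66.3% | −0.1 |
| 1/0.6/0.3 | 0.5 | 76.3% | 80.2% | 81.9% | +1.7 |
| 1/0.6/0.3 | 1.0 | 60.1% | 62.4% | 63.4% | +1.0 |
| 1/0.5/0.15 | 0.5 | 64.9% | 72.6% | 77.2% | +4.6 |
| 1/0.5/0.15 | 1.0 | 47.4% | 51.7% | 55.2% | +3.5 |

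(Differences are taken before rounding.) With no diet effect, type I error without a therapy term was 0.023 to 0.030. The simulation error at 0.025 is about √(0.025 × 0.975 / 1500) = 0.004, so this agrees with the nominal level.

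A separate simulation (37 per arm, 25/45/30% mix, dispersion 1 and 2, 4,000 runs) gave these gains of three levels over yes/no: about 0 points if group B has 25% fewer new lesions than the rest, +1 to +2 at 50% fewer, and +4 to +6 at 70% fewer.

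**4. Chance imbalance, given the stratification.** Assume 25% untreated, 45% group A and 30% group B. Stratifying on yes/no holds treated patients at about 0.75 × 37 = 27.75 per arm, of whom 0.30 / 0.75 = 40% are in group B. A gap of 15 points of the arm is 5.55 patients, so 6 or more; a gap of 20 points is 7.4, so 8 or more. For the difference of two independent Binomial(27 or 28, 0.4) counts:

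- 15 points or more: 12.6% (27 treated) to 13.3% (28 treated).
- 20 points or more: 3.6% to 4.0%.

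Ignoring the stratification, with Binomial(37, 0.3) counts, would give 16.2% and 5.6%. Those figures would overstate the imbalance in this trial.

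**The case against.** The strongest reply is that nothing here is wrong: the Discussion sentence is true of strata, the primary model is usable, and extra covariates can be left to an analysis plan that is not shown. The first two parts stand. The third stands only in part, because the article does not leave the primary model open; it names the covariate.

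A reader might infer three stronger things, which the text does not support.

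- *That stratification was the only remedy considered.* Restriction was considered and rejected, with generalisability and transferability to routine care given as further reasons for mixing therapies. Therapy must be stable or absent for 6 months before entry, a change of therapy is a discontinuation criterion, and an exploratory medication model is planned.
- *That mixed medication is the main source of heterogeneity.* It is listed first among critical aspects, but is neither ranked nor quantified.
- *That imbalance of drug types biases the diet comparisons.* Under randomisation such imbalance is random error, which the test already allows for, and the simulated type I error agrees.

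Nor is the trial shown to be underpowered: its 80% rests on a covariate-free test, which the article calls conservative. It is also fair that the gain may be nil. None of these safeguards, however, puts therapy into the confirmatory test, and the exploratory model pools all drugs.

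**Conclusion.** The point holds as a modest, inexpensive improvement to a stated model. The primary rank ANCOVA leaves out a baseline variable that the protocol stratifies on, records and names as a weakness, and the reason given does not exclude adjusting for it. The consequence is lost precision and unadjusted chance imbalance among treated patients; the test remains valid.

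The size depends on the drug mix and drug effects, neither of which the article gives. Over the assumptions tried, three levels add about 0 to 6 power points to a yes/no term. Compared with no therapy term at all, three levels add about 1 point with mild drug effects (65.0% to 66.3%) and up to 12 with the strongest assumed (64.9% to 77.2%); yes/no alone captures part of this. If therapy is not prognostic, about one point is lost.

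**What to change.** In the Data analysis section, add baseline MS therapy as a covariate in the primary rank ANCOVA. At a minimum use the yes/no stratification factor. Preferably use three levels, none plus two drug groups, which contain the yes/no factor. The investigators define the groups, blind to outcome data, before database lock. Many small drug categories should be avoided with about 99 evaluable patients (3 × 33).

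Put the same variable in the multiple imputation model. The plan triggers imputation above 5% missing and expects about 10% dropout, so imputation is likely to be needed. A sensitivity analysis alone would be informative but would leave the confirmatory test unchanged.

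In the Discussion, add that differences between therapies are handled by covariate adjustment because finer stratification was not feasible.

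Cost: a few lines of text, a grouping agreed in advance, and one or two degrees of freedom. No extra patients or data are needed.

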## Trial status

This article is based on the study protocol version 1.4 of 23 September 2019. The NAMS started on 24 May 2017. Recruitment will probably continue until March 2020.

## Data Availability

Not applicable.

## Abbreviations

EDSS: Expanded Disability Status Scale
FD: Fasting diet
ICH-GCP: International Conference on Harmonization of Good Clinical Practice
KD: Ketogenic diet
MRI: Magnetic resonance imaging
MS: Multiple sclerosis
NAMS: Nutritional Approaches in Multiple Sclerosis
QoL: Quality of life
RRMS: Relapsing–remitting multiple sclerosis
SD: Standard diet
